### Sample size

The trial will provide a comparison of tolerability between the modified schedule (Arm A) and standard schedule (Arm B) and will provide supportive data regarding the efficacy of the modified schedule (Arm A) in relation to historical control data with sunitinib [5]. To warrant further investigation, the modified schedule must meet both elements of the primary objective and show potential in terms of both tolerability and efficacy. In total, 189 patients (allowing for 5% attrition) will be recruited in order to adequately power both the toxicity and efficacy aspects of the study.

#### Toxicity

We expect approximately 40% of participants to experience a grade 3 or 4 AR within the initial 12 months of treatment when treated with the standard schedule (Arm B) [18]. To detect a clinically relevant reduction to 22% with the modified schedule (Arm A) (equivalent to a 45% relative reduction; odds ratio (OR) = 0.423), with 80% power at the two-sided 10% significance level, would require 178 participants, allowing for 5% attrition.

#### Efficacy

Assuming exponential survival, a median progression-free survival (PFS) with sunitinib of 9 months [5], (equivalent to 39.7% patients progression-free at 12 months) and targeting a minimum clinically relevant hazard ratio of 0.73 (corresponding to a median PFS in the modified Arm A schedule of 12.3 months, or 50.9% progression-free at 12 months) 120 participants would be required in the modified schedule arm to give 80% power at the one-sided 5% significance level. With 2:1 randomisation, a total of 189 patients will need to be recruited to allow for 5% attrition. Comparison with historical control data is based on data available at the time of design from the COMPARZ study [5], however additional unpowered analyses will be considered in light of the CM214 results now being available.

### Consent, eligibility, screening and registration

Potential participants from participating NHS hospitals in the UK will be provided with verbal and written information about the trial and given as long as required to consider participation. Assenting patients will provide written informed consent and be registered to the trial via a central automated 24-h system (provided by University of Leeds) prior to any trial specific assessments being conducted. Participants can also optionally consent to take part in HR-QoL and biomarker sub-studies. Participants retain the right to withdraw at any time without giving reasons and without their further treatment being prejudiced.

A full list of inclusion and exclusion criteria can be found in Table 1. In short, patients aged 18 or over with advanced or metastatic clear cell RCC, RECIST measurable disease and a Karnofsky Performance Status of at least 70% will be eligible. All IMDC risk-groups, including those with favourable-risk disease, are eligible. Patients will not be eligible if they have undergone prior systemic anti-cancer treatment or if they have active, known or suspected autoimmune disease. Eligibility waivers will not be granted in this trial.

**Table 1 Tab1:** Eligibility Criteria

Inclusion criteria	
Aged 18 years or over	
Diagnosed with advanced (not amenable to curative surgery) or metastatic RCC	
Histopathologically confirmed clear cell renal cell cancer (or with a component of clear cell)	
Evidence of measurable disease as per RECIST v1.1	
Life expectancy of ≥6 months	
Karnofsky Performance Status (KPS) of at least 70%	
Required laboratory values within 14 days prior to randomisation: • WBC ≥ 2 × 10^9^/L • Neutrophils ≥1.5 × 10^9^/L • Platelets ≥100 × 10^9^/L • Haemoglobin > 9.0 g/dL • Serum creatinine ≤1.5 x ULN or calculated creatinine clearance (CrCl) ≥ 40 mL/min (Cockcroft and Gault or Wright formula may be used according to local practice) • AST and ALT ≤3 x ULN • Total Bilirubin ≤1.5 x ULN (except subjects with Gilbert Syndrome, who can have total bilirubin < 50 μmol/L)	
Able to give written informed consent and willing to follow trial protocol	
Women of childbearing potential (WOCBP) must: • Use appropriate method(s) of contraception for 23 weeks after the last dose of investigational drug. • Have a negative serum or urine pregnancy test (minimum sensitivity 25 IU/L or equivalent units of HCG) before randomisation.	
Men who are sexually active with WOCBP must agree to use any contraceptive method with a failure rate of less than 1% per year. Men who are sexually active with WOCBP must agree to adhere to contraception for a period of 31 weeks after the last dose of investigational product.	
Exclusion criteria	
Pregnant or breast feeding females.	
Prior systemic therapy for RCC (previous participation in adjuvant studies allowed, providing the patient was on the observation/placebo arm – this may require unblinding of the patient)	
Participants who have undergone any prior systemic anti-cancer treatment, including with an anti-PD-1, anti-PD-L1, anti-PD-L2, anti-CTLA-4 antibody, or any other antibody or drug specifically targeting T-cell co-stimulation or immune checkpoint pathways (previous participation in adjuvant studies allowed, providing the patient was on the observation/placebo arm – this may require unblinding of the patient)	
Prior malignancy active within the previous 3 years except for locally curable cancers that have been apparently cured, such as basal or squamous cell skin cancer, superficial bladder cancer, or carcinoma in situ of the prostate, cervix, or breast.	
Participants who test positive for hepatitis B virus surface antigen (HBV sAg) or hepatitis C virus ribonucleic acid (HCV antibody) indicating acute or chronic infection.	
Participants who test positive for human immunodeficiency virus (HIV) or have known acquired immunodeficiency syndrome (AIDS).	
Untreated brain metastases or brain metastases treated only with whole brain radiotherapy. (Patients are eligible if previous brain metastases treated with complete surgical resection, Stereotactic Brain Radiation Therapy (SBRT), or gamma knife with no subsequent evidence of progression and asymptomatic).	
Active, known or suspected autoimmune disease. (Subjects are permitted to enrol if they have vitiligo, type I diabetes mellitus, residual hypothyroidism due to autoimmune condition only requiring hormone replacement, psoriasis not requiring systemic treatment, or conditions not expected to recur in the absence of an external trigger).	
Patients should be excluded if they have a condition requiring systemic treatment with either corticosteroids (> 10 mg daily prednisone or equivalent) or other immunosuppressive medications within 14 days of study drug administration. (Inhaled or topical steroids and adrenal replacement doses > 10 mg daily prednisone equivalents are permitted in the absence of active autoimmune disease).	
Uncontrolled adrenal insufficiency.	
Any serious or uncontrolled medical disorder that, in the opinion of the investigator, may increase the risk associated with study participation or study drug administration, impair the ability of the subject to receive protocol therapy, or interfere with the interpretation of study results.	
Palliative radiotherapy less than 14 days prior to first dose of study drug.	
Any history of hypersensitivity to any of the trial medications or excipients.	
Poorly controlled or serious medical or psychiatric illness that, in the Investigator’s opinion, is likely to interfere with participation and/or compliance in this clinical trial.	

Screening assessments for eligibility will include: Computed tomography (CT) chest, abdomen and pelvis; electrocardiogram (ECG); physical exam and medical history; full blood count (FBC); urea and electrolytes (U&Es); liver function tests (LFTs); hepatitis B/C and human immunodeficiency virus (HIV) tests; calculated creatinine clearance (CrCI); Karnofsky performance status (KPS); IMDC prognostic group classification; where applicable, pregnancy test. Consenting patients will also be asked to complete baseline HR-QoL questionnaires. Those assenting will also give samples of serum and plasma (and at selected sites only, peripheral blood mononuclear cells [PBMCs]).

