Recently (during the set-up of PRISM), initial results from the landmark phase III trial, CheckMate 214 (CM214) comparing nivolumab plus the anti-CTLA-4 antibody ipilimumab against standard of care sunitinib, have been reported. In total, 1096 participants with untreated metastatic clear cell RCC were randomised 1:1 to receive either sunitinib (50 mg 4 weeks on; 2 weeks off) or combination immunotherapy using a schedule of nivolumab 3 mg/kg (N3) plus ipilimumab 1 mg/kg (I1) every 3 weeks for 4 doses, followed by nivolumab 3 mg/kg every 2 weeks until disease progression or toxicity warranting treatment discontinuation [6]. Amongst the 77% of participants with intermediate- or poor-risk disease, as per International Metastatic Renal Cell Carcinoma Database Consortium (IMDC) criteria [7], median OS was not reached in the N3 + I1 arm and was 26.0 months in the sunitinib arm (HR 0.63, *p* < 0.001), establishing the combination as a new standard of care for the first-line treatment of patients with intermediate- and poor-risk mRCC [8]. Efficacy amongst favourable-risk participants formed an exploratory endpoint of the study and suggests improved response rates and PFS amongst sunitinib-treated patients, although these results should be interpreted with caution given the immature nature of the survival data and small sample size (*n* = 249). The reported toxicity associated with N3 + I1 was, however, significant. The rate of grade 3 or 4 treatment-related adverse events (AE) was 46% and led to treatment discontinuation in 22% of participants receiving the combination. In addition, high dose glucocorticoids (≥ 40 mg prednisone per day) were required in 35% of participants in order to manage immune-related AEs [6]. Until recently this combination treatment was not available in the UK, however it has gained approval for use in England through the national Cancer Drugs Fund in early April 2019 [9].

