#### Key secondary endpoint

Efficacy forms a key secondary endpoint of the study and will be based on the proportion of participants alive and progression-free at 12 months. Progression-free survival will be calculated from the date of randomisation to first documented evidence of disease progression (based on RECIST v1.1 criteria) or death. This landmark survival endpoint provides a pragmatic and timely readout of efficacy in this phase II trial and was selected before the results of the CM214 trial were available. Since the CM214 trial has now reported, additional exploratory analyses will be considered (such as the presentation of summary statistics for PFS at 12 m by prognostic group) and will be pre-specified prior to the final analysis being conducted.

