### Statistical methods and analysis

Analyses will be conducted following modified intention-to-treat principles (unless otherwise stated a priori) meaning participants will be analysed in the group to which they were randomised regardless of compliance or cross-over. Participants will be included in the primary and key secondary analyses provided they have received at least one dose of trial treatment and have provided the relevant outcome data.

The primary analysis will examine differences in the proportion of participants experiencing a grade 3 or 4 AR within the initial 12 months of treatment between trial arms using a logistic regression model, adjusting for minimisation factors (IMDC prognostic group, nephrectomy status, disease type); odds ratios will be presented alongside corresponding confidence intervals (CI). Pre-specified sensitivity analyses may be conducted as appropriate.

Should the primary analysis show a reduction in toxicity for the modified schedule (Arm A) compared with the standard schedule (Arm B), the formal key secondary analysis will be conducted. If the lower limit of the 90% CI for the proportion of participants alive and progression-free at 12 months in the modified schedule only (Arm A) excludes the rate of no interest based on historical (sunitinib-treated) control data (39.7%), the modified schedule will be deemed to have sufficient activity in line with that expected in the CM214 trial. The trial will provide supportive information rather than definitive conclusions of superiority of the modified arm to sunitinib.

Secondary endpoints will be analysed using summary statistics alongside confidence intervals where appropriate. All analyses will be fully detailed in a statistical analysis plan prior to being undertaken.

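### The single-arm efficacy test uses one pooled 39.7% sunitinib rate while all IMDC risk groups are eligible, so its error rates depend on a risk mix that the rule does not account for

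*Protocol article*

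**What the plan says.** - **Eligibility** (Consent, eligibility, screening and registration): "All IMDC risk-groups, including those with favourable-risk disease, are eligible". The article states no expected mix, cap or quota.
- **Benchmark** (Sample size, Efficacy): a 9-month median PFS on sunitinib, from one earlier trial, is "equivalent to 39.7% patients progression-free at 12 months". The target is a hazard ratio of 0.73, "corresponding to a median PFS in the modified Arm A schedule of 12.3 months, or 50.9% progression-free at 12 months". The risk mix of the source trial is not given.
- **Size** (same section): "120 participants would be required in the modified schedule arm to give 80% power at the one-sided 5% significance level", and "With 2:1 randomisation, a total of 189 patients will need to be recruited to allow for 5% attrition".
- **Decision rule** (Statistical methods and analysis): after a positive toxicity result, Arm A alone is judged to have enough activity if its lower 90% confidence limit "excludes the rate of no interest based on historical (sunitinib-treated) control data (39.7"%). No adjustment for risk group is described. The toxicity model, by contrast, adjusts for IMDC group.
- **Role of the result**: the Sample size section requires the modified schedule to succeed on both tolerability and efficacy before it goes further. The Statistical methods section describes the comparison with sunitinib as supportive and not definitive.
- **Risk-group results** (Key secondary endpoint): exploratory analyses, "such as the presentation of summary statistics for PFS at 12 m by prognostic group", are to be considered, and the article promises to pre-specify them before the final analysis.

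**The concern.** The article treats IMDC group as prognostic: it is a minimisation factor and a covariate in the toxicity model. For the randomised toxicity comparison, minimisation and adjustment deal with it. The efficacy comparison is not randomised, so it is more exposed to case mix, yet no such protection is stated for it. Minimisation makes Arm A resemble Arm B. It does nothing to make Arm A resemble the historical sunitinib patients.

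Two errors are possible. With proportionally more favourable-risk patients than in the source trial, a schedule no better than sunitinib within each risk group would pass too often. With fewer, a schedule that achieves the target effect would fail too often. The result helps decide whether the schedule is taken forward, so a conclusion driven by case mix would matter.

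**Working it through.** **1. The plan's own figures.** Under exponential survival, exp(−ln 2 × 12/9) = 39.7%; 0.397^0.73 = 50.9%; 9/0.73 = 12.3 months. The one-sample normal approximation gives

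n = [(1.645·√(0.397×0.603) + 0.842·√(0.509×0.491)) / (0.509 − 0.397)]² = 119.7, i.e. 120.

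The total is 120 × 1.5/0.95 = 189.5, against 189 stated. The design arithmetic is sound.

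**2. The rule as a count.** With 120 evaluable in Arm A, the smallest count whose 90% lower limit exceeds 39.7% is 57 (47.5%): the Wald limit is 40.0% and the Wilson limit 40.1%; at 56 they are 39.2% and 39.3%. P(X ≥ 57 | 0.397) = 5.0% and P(X ≥ 57 | 0.509) = 79.9%. An exact interval would need 58, with a false-positive rate of 3.4% and power of 74.3%. The rest uses 57.

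**3. Assumptions, not in the article.**
- Historical favourable share: 22.7%. This is 249/1096 from the phase III trial of nivolumab plus ipilimumab against sunitinib, the only mix in the article. It is not the mix of the trial that supplied the 39.7%.
- Gap g in sunitinib 12-month PFS between favourable and intermediate/poor risk: 10, 20 or 30 points.
- Favourable share m in Arm A: 10%, 30% or 40%.

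**4. Formulas.** Intermediate/poor rate = 0.397 − 0.227g; favourable rate = that plus g. The sunitinib-equivalent rate for Arm A's mix is p(m) = 0.397 + (m − 0.227)g. False-positive rate = P(X ≥ 57 | p(m)). Power = P(X ≥ 57 | p(m)^0.73).

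**5. Results.**

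| Gap | 30% favourable: p(m), false-positive rate | 40% favourable: p(m), false-positive rate | 10% favourable: p(m), power |
|---|---|---|---|
| 10 points | 40.4%, 7% | 41.4%, 10% | 38.4%, 72% |
| 20 points | 41.2%, 9% | 43.2%, 19% | 37.2%, 62% |
| 30 points | 41.9%, 12% | 44.9%, 31% | 35.9%, 52% |

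**6. Small case.** With a 10-point gap, a favourable share 10 points above the historical one gives a false-positive rate of about 8%. A share 10 points below gives power of about 73–74%.

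**The case against.** The strongest case on the other side is as follows.

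- **Case-mix mismatch is a general limit of historical-control phase II tests.** The article explains that a formal internal efficacy comparison was not feasible and calls the result supportive. That is fair, and it lowers the weight of the point. The same section still attaches a conclusion about activity to passing the fixed threshold.
- **Risk-group PFS is already foreseen**, with pre-specification promised, and its detail belongs in an analysis plan not shown here. This stands as far as it goes. But the rule and its number are already fixed in the article, and summaries beside them do not change what counts as a pass.
- **The size rests on unknown quantities.** This stands. The historical mix and the PFS gap are assumed, and modest values give modest effects. The source trial may itself have enrolled all risk groups, in which case open eligibility would match it. Matching eligibility does not guarantee matching proportions, however.
- **The false-positive rates assume equality with sunitinib in every risk group.** The Background reports that exploratory favourable-risk data "suggests improved response rates and PFS amongst sunitinib-treated patients", though it urges caution because the data are immature and the group small. If Arm A were worse than sunitinib in favourable risk, the inflation would shrink. With a 20-point gap and 40% favourable, an illustrative hazard ratio of 1.2 in that group only takes the 19% to about 8%, and 1.5 takes it to about 1.6%.

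A reader might infer that PRISM will recruit a different mix, because the combination became standard for intermediate and poor risk and was funded in England from April 2019. The article supports no direction: wider access outside the trial and the favourable-risk signal pull opposite ways. Nor does it show that 39.7% fails to describe the patients enrolled.

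**Conclusion.** The concern holds as a vulnerability of the stated rule, not as a demonstrated bias. Arm A's unadjusted proportion is tested against one pooled rate of unstated risk mix, all risk groups are eligible, and minimisation cannot protect a comparison that leaves Arm B out. Under the assumptions above, the false-positive rate is about 7–12% at 30% favourable and 10–31% at 40%, against a nominal 5%. Power is about 72–52% at 10% favourable, against 80%. These figures depend on an assumed 23% historical share, an assumed gap of 10 to 30 points and 120 evaluable patients; small shifts matter little.

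It would go too far to say that open eligibility is an error, that the sample size is wrong, or that the risk mix will decide the result. The documents support none of these. What they support is adding a check that shows whether the conclusion survives standardisation to the mix recruited.

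**What to change.** 1. Keep 39.7% as the formal threshold.
2. In Statistical methods and analysis, add a pre-specified sensitivity analysis. It compares Arm A with a sunitinib benchmark equal to the sum, over IMDC groups, of Arm A's observed share times that group's historical sunitinib 12-month PFS. Fix the group-specific rates before the final analysis, or a stated range of rates if the source trial used another risk score.
3. In Key secondary endpoint, commit to reporting Arm A's risk mix and its 12-month PFS with a 90% CI for favourable and for intermediate/poor risk. Keep this descriptive. With about 27 favourable-risk patients (23% of 120), the half-width is about 1.645 × √(0.55 × 0.45/27) = 16 points (taking a 55% rate), too wide for a subgroup gate.
4. If the standardised and unstandardised results disagree, state that the activity conclusion depends on case mix.

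**Cost:** analysis work and wording only. IMDC group is already recorded at screening, and no extra patients or visits are needed. The downsides are that the historical group rates are themselves uncertain and that a positive result may have to be worded more cautiously. A range of rates should inform the wording and not become a formal hurdle. At 40% favourable with a true 20-point gap, requiring success across gaps of 10 to 30 points would cut power from about 80% (tested against the matched benchmark) to about 68%.

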### Randomisation

Randomisation will be performed following confirmation of eligibility (and prior to any trial treatment) via a central automated 24-h system (provided by University of Leeds) to either the modified schedule or the standard schedule on a 2:1 allocation ratio in favour of the modified schedule. A computer–generated minimisation programme incorporating a random element generated by the independent CTRU Statisticians will be used to ensure treatment groups are well balanced proportionately with respect to: IMDC prognostic group (favourable/intermediate/poor risk); nephrectomy status (nephrectomy/no nephrectomy); and disease type (metastatic/locally advanced). Irrespective of their randomised allocation, participants should commence therapy within 14 days of randomisation.

### Assessments

A schedule of assessments is provided as supplementary material in (Additional file 2: Table S2).

#### During treatment

Due to the difference in treatment schedules, participants in Arm A (modified schedule) will be assessed every 2 weeks for the first 12 weeks while those in Arm B (standard schedules) will be assessed every 3 weeks until week 16. Thereafter, all participants will be assessed 4-weekly. Each assessment will include: clinical assessment; adverse event reporting; LFTs; FBC; U&Es; thyroid function test (TFT); glucose; calcium; amylase; and cortisol. PROMs will be completed at baseline and weeks 7, 13, and then 12-weekly until 61 weeks or until disease progression, whichever is earlier. Assenting participants will give samples of serum and plasma (and at selected sites only, PMBCs) at baseline, weeks 7, 13 and at disease progression.

The differential reporting between trial arms is not felt to be a large concern due to: i) the short time lapse between assessments; ii) there being only 1 week’s difference in the reporting period between trial arms; iii) follow-up being 4-weekly for both trial arms for the majority of the trial; and iv) the primary and key secondary endpoints being over 12 months. In addition, this differential follow-up is in favour of the standard schedule (Arm B) due to more frequent reporting in Arm A (modified schedule), and is therefore conservative.

All participants will receive radiological assessment according to RECIST criteria using contrast enhanced CT of the chest, abdomen and pelvis every 12 weeks until disease progression or treatment discontinuation (whichever occurs later).

